**Figure 1 figure1:**
[figure not shown]
The antistigma campaign material of the *Brilhar e Transcender* study.

### Study Procedures and Measures

Table 1 describes the study procedures. Potential participants are recruited by a community education team, through word of mouth, and via referrals from enrolled participants. Recruitment also occurs at the HIV prevention services based at our site and at an on-site mobile legal unit that offers weekly access to free legal services for transgender people.

Participants have 5 in-person encounters at the National Institute of Infectious Diseases Evandro Chagas, Fiocruz, including a screening and enrollment visit followed by 4 quarterly visits (at weeks 12, 24, 36, and 48). The BeT intervention takes place between the enrollment visit and the 12-week visit and is completed within that time frame. Trained staff conduct interviewer-administered surveys to participants at all study visits.

At baseline, all participants respond to a screening questionnaire and demographic information, after signing the written informed consent form. Baseline and quarterly survey content build upon questionnaires previously developed and tested with transgender women in Brazil and in the United States, as described in Table 2. During follow-up visits, we will collect information on study outcomes: HIV incidence, PrEP uptake and adherence among HIV-negative participants, and linkage to HIV care and viral load suppression among those living with HIV. In addition, we will also collect data on implementation science outcomes: (1) maintenance (pre- and poststudy) for study coordination, feasibility (poststudy) for peer health navigators, and feasibility, acceptability, and appropriateness (poststudy) for study participants.

**Table 1 table1:** Measures of the *Brilhar e Transcender* study.

Measures		Time frame	Source
Demographics		Baseline	Grinsztejn et al [6]
Transitioning process		Baseline and quarterly	Grinsztejn et al [6]
Food insecurity		Baseline and quarterly	Adapted from the Food and Agriculture Organization of the United Nations [35]

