### Eligibility Criteria

Inclusion criteria are (1) having been assigned the male sex at birth and self-identifying as *travesti*, a transgender woman, or having a gender identity different from identities typically associated with the assigned sex at birth; (2) being aged between 18 and 24 years; (3) providing consent for study participation; (4) living in Rio de Janeiro or the greater metropolitan area; and (5) being sexually active. Additional criteria for HIV-negative individuals include (1) no current PrEP use, (2) PrEP indication per Brazilian standards of care, and (3) no PrEP contraindication. For participants living with HIV, additional inclusion criteria are (1) having a confirmed HIV diagnosis, (2) not currently using antiretroviral therapy (ART) or having a detectable viral load and treatment that is not linked to HIV care.

Exclusion criteria include participation in any HIV prevention or care intervention study in the last year, refusal to undergo HIV testing, or having any health condition that, in the opinion of the investigator, precludes participation in the study or may lead to harm to the participant.

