**Laboratory procedures**													
	HIV rapid test	✓		✓^b^		✓^b^		✓^b^		✓^b^		✓	
	CD4^+^ and CD8^+^ cell counts	✓^c^				✓^c^				✓^d^		✓	
	HIV RNA viral load	✓^c,d^		✓^d^		✓^c,d^		✓^d^		✓^c,d^		✓	
	HIV recency testing	✓^c^										✓	
	HIV genotyping	✓^c^										✓	
	Treponemal syphilis rapid test	✓		✓		✓		✓		✓			
	Nontreponemal syphilis (venereal disease research laboratory) testing	✓^e^		✓^e^		✓^e^		✓^e^		✓^e^			
	Hepatitis B rapid test	✓								✓^f^			
	Hepatitis B serology	✓^g^											
	Hepatitis C rapid test	✓								✓^h^			
	Anti–hepatitis C virus	✓^i^								✓^i^			
	Hepatitis C viral load	✓^j^								✓^j^			
	Rectal swab (*Chlamydia trachomatis* and *Neisseria gonorrhoeae*)	✓								✓			
	Dried blood spot (pre-exposure prophylaxis adherence assessment)	✓^k^		✓^k^		✓^k^		✓^k^		✓^k^		✓^k^	
Hormone dispensation			✓		✓		✓		✓		✓		✓
Medical or psychiatric visit			✓^l^		✓^l^		✓^l^		✓^l^		✓^l^		

^a^Withdrawn or discontinued participants before the final visit.

^b^Only for participants with a negative HIV test in the previous visit.

^c^For all participants living with HIV.

^d^Only for HIV-negative participants with recent HIV exposition according to the service guidelines.

^e^Only for those with a positive treponemal test result.

^f^Only for a negative hepatitis B rapid test result.

^g^Only for a positive hepatitis B rapid test result.

^h^Only for those with a negative hepatitis C rapid test result.

^i^Only for those with a positive hepatitis C rapid test result.

^j^Only for those with positive findings on an anti–hepatitis C virus antibody test.

^k^Only for participants receiving pre-exposure prophylaxis, except those initiating pre-exposure prophylaxis at the current visit.

^l^If clinically indicated.

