### The BeT Intervention

The 3-month BeT intervention comprises three components: (1) BeT sessions, (2) digital interactions, and (3) automatic messages (Figure 2). During the first BeT session, the participant works with a peer navigator to build a case management plan aimed at meeting HIV prevention and care goals, and getting other needs met to promote health and wellness (BeT plan). BeT sessions 1 and 3 are conducted in person at enrollment and week 12 visits, respectively. BeT session 2 is conducted remotely via a mobile phone. Participants select a preferred app (eg, WhatsApp or Facebook messenger) for communicating asynchronously with the peer navigator during BeT session 2. Asynchronous digital interactions with peer navigators occurs at least weekly for 3 months and can be more frequent based on participant needs. Digital interactions were not restricted to study participation or HIV prevention or care and can include social support, food basket provisions, and guidance on employment, self-care, and other supports. Finally, participants received weekly automatic messages with health information on HIV testing, prevention, and care.

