### Statistical Analysis

Statistical analysis will assess recruitment, baseline, and follow-up data and will describe the rapidity of enrollment of young transgender women, their demographic and risk characteristics, and participation as the percent intervention uptake (ie, the number of participants in the BeT intervention divided by the total number of individuals who were assessed for participation and were preliminarily eligible for the study). We will describe PrEP uptake and adherence and HIV care service linkage at intervention initiation and completion. For the primary endpoint, we will compare PrEP uptake and adherence and HIV care linkage between baseline and follow-up data (ie, before and after the intervention). Primary analyses will test the hypothesis that the odds of PrEP uptake and adherence and HIV care linkage will be higher post intervention relative to baseline data. We anticipate behavior change within 3 instead of 6 months because of our ability to more frequently interact with participants (3 months). In fact, we may achieve a greater dose response and intervention effect in a shorter amount of time because of the possibility for a higher number of encounters. At minimum, participants will engage with their digital navigator 4 to 5 times a week in the form of short digital encounters, and over the course of the intervention, participants will have 48 to 60 short digital encounters in total. We will use a pooled logistic model to estimate treatment effects on time to PrEP uptake and adherence and HIV care linkage.

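### PrEP uptake starts from zero by eligibility and has no comparator, so the before/after test and the time-to-uptake model credit BeT with starts that would have happened anyway, including among recruits from the site's own HIV prevention service

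*Protocol article*

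**What the plan says.** All references are to the protocol article.

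- **Entry.** Under Eligibility Criteria, HIV-negative participants must have "no current PrEP use, (2) PrEP indication per Brazilian standards of care".
- **Recruitment.** Under Study Procedures and Measures, "Potential participants are recruited by a community education team, through word of mouth, and via referrals from enrolled participants". The section adds: "Recruitment also occurs at the HIV prevention services based at our site". An on-site legal unit is a further route. No shares are given.
- **Enrollment visit.** Screening and enrollment are one visit. Under The BeT Intervention, "BeT sessions 1 and 3 are conducted in person at enrollment and week 12 visits, respectively".
- **Possible same-visit start.** In Table 2 (schedule of events), footnote k to the dried-blood-spot row, which also marks the baseline column, reads: "Only for participants receiving pre-exposure prophylaxis, except those initiating pre-exposure prophylaxis at the current visit".
- **Primary analysis.** Under Statistical Analysis: "Primary analyses will test the hypothesis that the odds of PrEP uptake and adherence and HIV care linkage will be higher post intervention". The contrast is with baseline. Uptake is also to be described at the start and at the end of the intervention. A pooled logistic model of time to uptake is said to estimate treatment effects.
- **External comparison.** The same section limits it to people who have initiated PrEP or ART and expressly does not assess uptake.
- **Limitations.** The Discussion offers the before/after change and the external group as the answer to having no randomization. It treats the convenience sample only as a limit on applicability.

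**The concern.** A before/after contrast measures an intervention's effect only if the outcome would have stayed at its baseline level without the intervention. For PrEP uptake that cannot be assumed here. The baseline level is fixed at zero by the entry criteria, all HIV-negative entrants have a PrEP indication, and some were found at a service that exists to provide HIV prevention. Some of them might have started PrEP without a peer navigator. The analysis has no means of separating those starts from starts that BeT produced. The safeguard named in the Discussion, the external group, is not applied to this outcome.

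At stake is whether a positive primary result can support the statement that BeT raised uptake by reducing barriers to prevention. The unclear status of a start at the enrollment visit adds to this, because the two possible classifications move the before/after contrast in opposite directions.

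**Working it through.** **The plan's own figure.** Sample Size and Power Calculation states 80% power, two-sided 5%, for increases of 10 to 15 percentage points in binary responses, with 150 enrolled and 15% attrition (150 × 0.85 = 127.5, taken as 127). A paired (McNemar, normal approximation) calculation at n = 127, with within-subject correlation from 0.4 down to 0, gives detectable increases of:

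- 10.0 to 13.2 points at 10% baseline frequency
- 12.2 to 15.9 points at 20%
- 13.7 to 17.4 points at 50%

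The stated range is plausible. It cannot be reproduced exactly, because the baseline frequency and correlation are not given. It does not bear on attribution.

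**Step 1: what zero at entry does.** With no users at baseline, every discordant pair is a start. The exact two-sided McNemar p-value for b starters is 2 × 0.5^b.

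- b = 5: 2 × 0.5^5 = 0.0625
- b = 6: 2 × 0.5^6 = 0.031

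Six starters are enough. McNemar stands in here for the planned before/after comparison of odds.

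**Step 2: how small six is.** The article does not give the number of HIV-negative participants. As an assumption, take the 24.2% HIV prevalence quoted in the Introduction for ages 18 to 24, with a range of 10% to 40%.

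- 24.2%: 150 × 0.758 = 114 HIV-negative; × 0.85 = 97 retained; 6/97 = 6.2%
- 10%: 135 HIV-negative; 115 retained; 6/115 = 5.2%
- 40%: 90 HIV-negative; 76 retained; 6/76 = 7.9%

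**Step 3: chance of a significant gain when BeT adds nothing.** Let u be the proportion who would have started anyway. The probability is P(Bin(n, u) ≥ 6).

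| u (assumed) | n = 115 | n = 97 | n = 76 |
|---|---|---|---|
| 5% | 0.52 | 0.36 | 0.18 |
| 10% | 0.98 | 0.93 | 0.78 |
| 15% | >0.99 | >0.99 | 0.98 |

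**Step 4: link to the recruitment route.** Suppose a share s of HIV-negative participants comes from the service, a fraction q of these would start anyway, and nobody else would. Then u = s × q. At n = 97:

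- s = 10%, q = 30%: u = 3%, probability 0.07
- s = 10%, q = 50%: u = 5%, probability 0.36
- s = 20%, q = 50%: u = 10%, probability 0.93
- s = 30%, q = 50%: u = 15%, probability above 0.99

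Neither s nor q is in the article. The effect of this route on the test could be slight or decisive.

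**Step 5: the same-day start.** Eligibility requires "no current PrEP use", and outcomes are collected at follow-up visits, which points to counting an enrollment-visit start as post-intervention. The article also plans to describe uptake at intervention initiation, which could make it baseline status. Under the first reading, same-day starts enter as the earliest successes. Under the second, they leave the gain altogether, including any that session 1 prompted. The article does not choose between them.

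**The case against.** A reader might infer that service recruits start PrEP on day 0, that these starts would largely happen without BeT, and that they are counted as its product. The article does not support that chain.

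- Footnote k is attached to the whole row, including the seroconversion visit. Its exception, "except those initiating pre-exposure prophylaxis at the current visit", is a sampling rule. It shows that a same-visit start is possible, not that it is common, and no methods text says that PrEP begins at enrollment.
- Session 1 takes place at that visit, with a navigator building a plan towards prevention goals. Part of any same-day uptake may be BeT's doing.
- Attending a prevention service is not the same as having overcome the barriers. Eligible attendees are PrEP-indicated and still not on it, and the Introduction describes stigma and low knowledge that attendance does not remove.
- Describing uptake at initiation is already planned.

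These points stand, and they limit the concern.

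It can also be said that steps 1 to 3 follow from zero use at entry and the lack of a control whatever the route, that non-randomization is acknowledged, and that leaving uptake out of the external comparison is disclosed with a reason. This is correct, and it means that tabulating by route cannot by itself repair attribution. It does not remove the problem: disclosure supplies no comparator, and the treatment-effect wording remains.

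Finer detail may sit in a statistical analysis plan that is not shown. But the contrast, its causal wording and the exclusion of uptake from the external comparison are all fixed in the article itself.

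**Conclusion.** The concern holds as a problem of attribution. Uptake is zero at entry by design, some entrants come from the site's own prevention service, and uptake has no comparator, so starts that would have occurred anyway are credited to BeT.

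The size is unknown. The 0.93 figure assumes 10% background uptake, 24.2% HIV prevalence, 15% attrition applied to the HIV-negative group, and a McNemar test in place of the planned model. It is an illustration, not an estimate. At 5% background uptake the probability falls to between 0.18 and 0.52.

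A reader might also try to size the effect by assuming that every service recruit starts on day 0 and that 20% of the others start. Overall uptake is then s + (1 − s) × 0.20, or 36%, 52% and 68% for service shares s of 20%, 40% and 60%. All of these inputs are assumed, and the result does not show how many would have started without BeT.

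The classification of a same-day start is open in the text and must be settled. The point concerns uptake only: PrEP and ART adherence and viral suppression do have an external comparison.

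**What to change.** 1. State whether a PrEP start at the enrollment visit counts as baseline or post-intervention, and apply that in both the before/after comparison and the time-to-uptake model.
2. Report uptake in two parts: started at the enrollment visit, and started after it, by week 12.
3. If recruitment route was recorded, which the article does not say, tabulate both parts by route (site HIV prevention service versus other routes), descriptively and with confidence intervals. Resting the conclusion about barriers only on participants from outside the service is debatable and is not asked for here; the legal unit, for example, is also on site.
4. Describe the before/after result as uptake among enrolled participants, and drop the treatment-effect wording for this outcome. This step addresses the missing comparator; steps 1 to 3 make the components visible.

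The cost is analysis and reporting text, with no change to study procedures. It needs start dates and, for step 3, recruitment route to be retrievable. The downside is small strata, wide intervals and a less favourable headline.

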**Substance use**			
	Alcohol Use Disorders Identification Test for alcohol consumption (3 items)	Baseline and quarterly	Bush et al [36]
	Alcohol, Smoking and Substance Involvement Screening Test	Baseline and quarterly	World Health Organization [37]
Stigma and discrimination (including transgender-specific health care discrimination)		Baseline and quarterly	Grinsztejn et al [6], Costa et al [15], and Scandurra et al [38]
Violence		Baseline and quarterly	Grinsztejn et al [6]
Overall health issues		Baseline and quarterly	Grinsztejn et al [6]
Medical mistrust (12-item Group-Based Medical Mistrust Scale)		Baseline and quarterly	Adapted from Thompson et al [39]
Medical avoidance		Baseline and quarterly	Adapted from James et al [40]
HIV knowledge and attitudes (10-item HIV Knowledge Questionnaire adapted to 8 items, HIV testing and counseling attitudes and knowledge)		Baseline and quarterly	Oglesby and Alemagno [41] and Kalichman and Simbayi [42]
Self-efficacy			Adapted from Zhao et al [43]
HIV testing, prevention, and care		Baseline and quarterly	Grinsztejn et al [6]
HIV perceived risk index		Baseline and quarterly	Lauby et al [44]
Testing and diagnosis of sexually transmitted infections		Baseline and quarterly	Grinsztejn et al [6]
Adherence (adapted to antiretroviral therapy and pre-exposure prophylaxis)		Baseline and quarterly	Adapted from Wilson et al [45]
Overall mental health assessment and suicide		Baseline and quarterly	Grinsztejn et al [6] and Jalil et al [46]
The Patient Health Questionnaire for Depression and Anxiety scale		Baseline and quarterly	Kroenke et al [47]
The Primary Care Posttraumatic Stress Disorder scale		Baseline and quarterly	Prins et al [48]
Social support (Multidimensional Scale of Perceived Social Support)		Baseline and quarterly	Zimet et al [49]
Resilience (2-item Connor-Davidson Resilience scale)		Baseline and quarterly	Connor and Davidson [50]
Brazilian political context		Baseline and quarterly	The authors of this study
Sexual behavior		Baseline and quarterly	Adapted from Rocha et al [51]

**Table 2 table2:** Schedule of events of the *Brilhar e Transcender* study.

			Baseline		Week 12		Week 24		Week 36		Week 48 or early termination^a^		HIV seroconversion visit
Eligibility			✓										
**Measures**													
	Behavioral, partnership, network, and structural measures	✓		✓		✓		✓		✓		✓	
	Adverse events			✓		✓		✓		✓			
	Social harm			✓		✓		✓		✓			
	Implementation science: participants									✓			
	Implementation science: coordination	✓								✓			
	Implementation science: peer navigators									✓			
**Laboratory procedures**													
	HIV rapid test	✓		✓^b^		✓^b^		✓^b^		✓^b^		✓	
	CD4^+^ and CD8^+^ cell counts	✓^c^				✓^c^				✓^d^		✓	
	HIV RNA viral load	✓^c,d^		✓^d^		✓^c,d^		✓^d^		✓^c,d^		✓	
	HIV recency testing	✓^c^										✓	
	HIV genotyping	✓^c^										✓	
	Treponemal syphilis rapid test	✓		✓		✓		✓		✓			
	Nontreponemal syphilis (venereal disease research laboratory) testing	✓^e^		✓^e^		✓^e^		✓^e^		✓^e^			
	Hepatitis B rapid test	✓								✓^f^			
	Hepatitis B serology	✓^g^											
	Hepatitis C rapid test	✓								✓^h^			
	Anti–hepatitis C virus	✓^i^								✓^i^			
	Hepatitis C viral load	✓^j^								✓^j^			
	Rectal swab (*Chlamydia trachomatis* and *Neisseria gonorrhoeae*)	✓								✓			
	Dried blood spot (pre-exposure prophylaxis adherence assessment)	✓^k^		✓^k^		✓^k^		✓^k^		✓^k^		✓^k^	
Hormone dispensation			✓		✓		✓		✓		✓		✓
Medical or psychiatric visit			✓^l^		✓^l^		✓^l^		✓^l^		✓^l^		

^a^Withdrawn or discontinued participants before the final visit.

^b^Only for participants with a negative HIV test in the previous visit.

^c^For all participants living with HIV.

^d^Only for HIV-negative participants with recent HIV exposition according to the service guidelines.

^e^Only for those with a positive treponemal test result.

^f^Only for a negative hepatitis B rapid test result.

^g^Only for a positive hepatitis B rapid test result.

^h^Only for those with a negative hepatitis C rapid test result.

^i^Only for those with a positive hepatitis C rapid test result.

^j^Only for those with positive findings on an anti–hepatitis C virus antibody test.

^k^Only for participants receiving pre-exposure prophylaxis, except those initiating pre-exposure prophylaxis at the current visit.

^l^If clinically indicated.

### The BeT Intervention

The 3-month BeT intervention comprises three components: (1) BeT sessions, (2) digital interactions, and (3) automatic messages (Figure 2). During the first BeT session, the participant works with a peer navigator to build a case management plan aimed at meeting HIV prevention and care goals, and getting other needs met to promote health and wellness (BeT plan). BeT sessions 1 and 3 are conducted in person at enrollment and week 12 visits, respectively. BeT session 2 is conducted remotely via a mobile phone. Participants select a preferred app (eg, WhatsApp or Facebook messenger) for communicating asynchronously with the peer navigator during BeT session 2. Asynchronous digital interactions with peer navigators occurs at least weekly for 3 months and can be more frequent based on participant needs. Digital interactions were not restricted to study participation or HIV prevention or care and can include social support, food basket provisions, and guidance on employment, self-care, and other supports. Finally, participants received weekly automatic messages with health information on HIV testing, prevention, and care.

**Figure 2 figure2:**
[figure not shown]
Intervention components of the Brilhar e Transcender study.

### Statistical Analysis

Statistical analysis will assess recruitment, baseline, and follow-up data and will describe the rapidity of enrollment of young transgender women, their demographic and risk characteristics, and participation as the percent intervention uptake (ie, the number of participants in the BeT intervention divided by the total number of individuals who were assessed for participation and were preliminarily eligible for the study). We will describe PrEP uptake and adherence and HIV care service linkage at intervention initiation and completion. For the primary endpoint, we will compare PrEP uptake and adherence and HIV care linkage between baseline and follow-up data (ie, before and after the intervention). Primary analyses will test the hypothesis that the odds of PrEP uptake and adherence and HIV care linkage will be higher post intervention relative to baseline data. We anticipate behavior change within 3 instead of 6 months because of our ability to more frequently interact with participants (3 months). In fact, we may achieve a greater dose response and intervention effect in a shorter amount of time because of the possibility for a higher number of encounters. At minimum, participants will engage with their digital navigator 4 to 5 times a week in the form of short digital encounters, and over the course of the intervention, participants will have 48 to 60 short digital encounters in total. We will use a pooled logistic model to estimate treatment effects on time to PrEP uptake and adherence and HIV care linkage.

We will also assess outcomes comparing data from the external comparison group to the BeT intervention group. First, we will conduct sensitivity analyses to compare the demographics of our intervention group to those of the external comparison group. In the analysis, we will focus on comparisons between the BeT intervention group and the external comparison group on measures of PrEP and ART adherence and viral suppression. Primary analyses will involve intention-to-treat analysis without considering adherence to the BeT intervention. This analysis will be a comparison of initiators of PrEP and ART, and we shall adjust for baseline confounders related to age or race. We have chosen to compare initiators of PrEP or ART and not assess PrEP uptake because a comparison of initiators parallels intention-to-treat analysis in which assignment and initiation of the treatment strategies occur together at baseline, regardless of whether individuals continue on the strategies after baseline [52]. We will combine outcome estimates with the cost estimates of the intervention component to calculate cost per participant and roughly estimate costs per HIV infection averted or poor health outcomes based on cohort data being collected in Brazil on HIV incidence and care outcomes.

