**Methods:**

The *Brilhar e Transcender* (BeT) study is a status-neutral, peer-led, single-arm digital intervention study enrolling 150 young transgender women in Rio de Janeiro, Brazil. The intervention was pilot tested and refined using data from a formative phase. The BeT intervention takes place over 3 months, is delivered remotely via mobile phone and in person by peers, and comprises three components: (1) BeT sessions, (2) digital interactions, and (3) automated messages. Eligibility criteria include identifying as transgender women, being aged 18-24 years, speaking in Portuguese, and living in the Rio de Janeiro metropolitan area in Brazil. The primary outcomes are HIV incidence, pre-exposure prophylaxis uptake, linkage to HIV care, and viral suppression. Primary outcomes were assessed at baseline and quarterly for 12 months. Participants respond to interviewer-based surveys and receive tests for HIV and sexually transmitted infections.

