### Formative Phase

The study had a formative phase, which comprised developing and implementing an antistigma campaign, and adaptation and pilot testing of the system navigation intervention [32]. The campaign content included information on basic gender definitions (sex, gender identity, gender expression, and sexual orientation), regulations linked to gender and sexual orientation minorities, the medical transition process, overview of mental health and hormone therapy among transgender people, transphobia and violence against transgender people, and HIV among transgender women (Figure 1). The antistigma campaign, focused on health care settings, clinical providers, and support staff, took place at 4 health clinics serving transgender women in Rio de Janeiro, Brazil. We collected pre- and postcampaign qualitative and quantitative data with providers (N=10) to assess whether antitransgender stigma beliefs and attitudes changed among providers and support staff.

We also conducted formative qualitative interviews with 10 young transgender women (mean age 22.2 years) to inform the development of the pilot intervention. The BeT study uses an effective US Centers for Disease Control and Prevention intervention called *Anti-Retroviral Treatment and Access to Services* for system navigation and linkage [33,34]. Three components of the intervention required adaptation: (1) content of the Anti-Retroviral Treatment and Access to Services intervention session plan and asynchronous interactions with young transgender women, (2) adaptation to the cultural context of Brazil, and (3) the digital interface. Ten young transgender women were recruited through community outreach by our community engagement specialists (n=2) and through referrals from other studies at Fiocruz (n=8).

The BeT study pilot-assessed the intervention’s preliminary efficacy among 20 participants. Results from the pilot intervention demonstrated preliminary efficacy for improving HIV prevention and care behaviors among young transgender women, as all HIV-negative participants were engaged in PrEP and all but one participant living with HIV became virally suppressed [32]. After the pilot phase, the team refined the intervention, which focused on streamlining the adapted intervention manual to improve peer navigator and participant accessibility. In addition, the team added additional medical monitoring to include important biomarkers of sexual health and HIV as part of the study protocol.

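### The before/after primary test cannot show a BeT effect on PrEP uptake, because eligibility fixes baseline use at zero; adherence has no baseline value, and change in linkage is biased upward

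*Protocol article*

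**What the plan says.** The abstract describes a "status-neutral, peer-led, single-arm digital intervention study enrolling 150 young transgender women", so there is no concurrent control. Under Statistical Analysis, the primary endpoint compares PrEP uptake, PrEP adherence and HIV care linkage before and after the intervention. The hypothesis is that "the odds of PrEP uptake and adherence and HIV care linkage will be higher post intervention relative to baseline data". The same section adds a pooled logistic model for treatment effects on time to these outcomes.

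Eligibility Criteria sets the starting state. For HIV-negative people: "Additional criteria for HIV-negative individuals include (1) no current PrEP use, (2) PrEP indication per Brazilian standards of care, and (3) no PrEP contraindication". For people living with HIV: "not currently using antiretroviral therapy (ART) or having a detectable viral load and treatment that is not linked to HIV care".

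The schedule of events (Table 2, footnote k) limits the dried blood spot for PrEP adherence: "Only for participants receiving pre-exposure prophylaxis, except those initiating pre-exposure prophylaxis at the current visit".

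The external comparison in Statistical Analysis covers PrEP and ART adherence and viral suppression among people who start PrEP or ART. It says explicitly that PrEP uptake is not assessed there, and it does not list linkage. The Discussion acknowledges the lack of randomization and offers before/after change plus the external group as the remedy.

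**The concern.** A before/after test is informative only if the baseline value is a fair stand-in for what would have happened without the intervention. Here people are selected because they lack the outcome. Anyone who starts PrEP for any reason in the next 12 months moves the result in one direction, and nobody can move it the other way. Some starting without BeT is plausible: recruitment also takes place at the site's own HIV prevention services, and the Discussion describes oral PrEP as public policy in Brazil since 2017.

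At stake is the main claim. The Conclusions and Discussion look ahead to rapid scale-up if the evaluation is promising. A significant rise from a baseline set at zero would look like support for that without being evidence of an effect.

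**Working it through.** **The plan's own figure.** Sample Size and Power Calculation gives 80% power, two-sided 5%, for increases of 10-15 percentage points in binary responses, with 150 enrolled and 15% attrition (150 × 0.85 ≈ 127). It gives neither the baseline frequency nor the within-subject correlation, so I scanned both.

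Paired-proportion (McNemar) approximation, with δ the increase and s the proportion of discordant pairs: n = [1.96√s + 0.842√(s − δ²)]² / δ².

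- Correlation 0.2, n=127: δ = 9.6 points at baseline 5% and 14.2 points at baseline 20%.
- Correlation 0.4, n=127: δ = 10.0 points at baseline 10% and 13.7 points at baseline 50%.

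The stated range is compatible with these inputs, but it presumes a non-zero baseline. At baseline 0 the within-subject correlation is undefined.

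**PrEP uptake.** With baseline fixed at 0, every discordant pair goes from no to yes. The exact two-sided p-value with x starters is 2 × 0.5^x:

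- x = 5: 0.0625
- x = 6: 0.031

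So 6 starters reject. The article names no paired test; exact McNemar is used here to size the problem.

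Subgroup size is an assumption: 24.2% living with HIV, from the survey cited in the Introduction. HIV-negative: 150 × 0.758 ≈ 114, and 114 × 0.85 ≈ 97. Then 6/97 = 6.2%. With no BeT effect, the rejection probability is P(X ≥ 6) for X ~ Binomial(97, q), where q is the assumed background uptake:

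| q | P(reject), no BeT effect |
|---|---|
| 5% | 0.36 |
| 10% | 0.93 |
| 15% | 0.998 |

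If the HIV-positive share runs from 10% to 50% (115 down to 64 evaluable HIV-negative participants), 80% rejection needs background uptake of only 6.8% to 12.1%.

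**PrEP adherence.** An HIV-negative entrant is not on PrEP. Footnote k takes a sample only from people on PrEP who are not starting that day. No eligible entrant gives a baseline sample, so a before/after test is undefined, or has a zero entered by convention.

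**HIV care linkage.** HIV-positive: 150 × 0.242 ≈ 36, and 36 × 0.85 ≈ 31. If baseline linkage is 0, 6/31 = 19.4% is needed. Rejection with no BeT effect, Binomial(31, q):

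| Background linkage q | P(reject), no BeT effect |
|---|---|
| 10% | 0.08 |
| 20% | 0.61 |
| 30% | 0.94 |

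If 20% or 40% were already linked and stayed linked, 25 or 19 people remain who can change. Rejection at 30% background among them falls to 0.81 or 0.53. The subgroup size matters more here: at 20% background and baseline 0, the probability runs from 0.03 (HIV-positive share 10%, n=13) to 0.993 (share 50%, n=64).

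**What an informative null looks like.** For 97 HIV-negative participants and an assumed reference of 20%, at least 28/97 (28.9%) is needed (exact one-sided alpha 0.023), with 80% power at a true 32.4%. For a reference of 40%, the figures are 49/97 (50.5%) and 54.3%.

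**The case against.** Several points on the other side stand.

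- **Linkage is not fixed at zero.** The HIV-positive criterion joins its parts with an or and an and. If being off ART is enough to enter, someone already linked could enrol and later drop out. Baseline linkage is zero on one reading only.
- **Adherence has a comparator.** The external comparison covers PrEP adherence among initiators.
- **A time-to-event model is also planned.** Nobody having the event at time zero is normal there and causes no separation. An infinite odds ratio arises only in a direct baseline-versus-follow-up contrast. The model does not supply the missing comparator, though: in a single arm all follow-up time comes after enrolment.
- **Uptake and linkage will also be described.** The plan already reports them at intervention initiation and completion, and the Discussion admits the lack of randomization. That admission does not help uptake, because the external group offered as the remedy excludes it.

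A reader might infer that the entry criteria decide all three primary results in advance, or that the data will say nothing about BeT. The documents do not support either. Six conversions are still needed, about 19% of the assumed linkage subgroup, and even for uptake a 5% background gives rejection only 0.36 of the time. The follow-up proportions remain useful description. A reader might also cite the pilot, where "all HIV-negative participants were engaged in PrEP and all but one participant living with HIV became virally suppressed", as proof that the test would reject regardless. Those results arose under the intervention and do not show background uptake.

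**Conclusion.** The concern holds, to a different degree for each outcome.

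- **PrEP uptake:** the primary before/after hypothesis is uninformative about BeT. This follows from the text alone: baseline is 0 by eligibility, change can only be upward, and there is no other contrast. The rejection probabilities rest on the assumed HIV-positive share, 15% attrition, the assumed background rates and the use of an exact paired test.
- **PrEP adherence:** the before/after test has no measured baseline. The only usable contrast is the external comparison among initiators.
- **HIV care linkage:** selecting people in a poor state biases the change upward, but the result is not predetermined. Linkage is not listed in the external comparison.

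This is not a detail left to a statistical analysis plan. The article itself states the hypothesis, the comparison and the entry criteria, and they do not fit together.

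**What to change.** For PrEP uptake and HIV care linkage, replace the baseline-versus-follow-up null test with estimation:

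1. Report the proportion achieving each outcome by week 12 and at week 48, among all enrolled participants in the relevant HIV-status group, with exact 95% confidence intervals. Handle missing data as the Missing Data section already sets out.
2. Judge each proportion against a non-zero reference fixed and justified before analysis or, if the data exist, against external-group members who meet the same entry criteria.
3. Report PrEP adherence as a follow-up proportion among all HIV-negative participants, and keep the planned external comparison among initiators.
4. State that change from baseline in these outcomes is not evidence of a BeT effect.
5. Clarify which reading of the HIV-positive entry criterion applies, so that baseline linkage can be described.

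No new visits or samples are needed. The cost is a less favourable headline result and the work of justifying a benchmark. The article does not show whether the external group includes people who did not start PrEP or ART, so that route may not be available.
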